### Additional outcomes

#### Personal and medical factors [baseline A phase; single timepoint]

Participants self-reported sociodemographic (age, gender identity, ethnicity, civil status, work/education status, income, and comorbidities), medical information (height, weight, cancer type and stage, type and protocol of treatments received for their cancer [i.e., surgery, chemotherapy, radiation, immunotherapy, hormonal]), and perceived physical and mental health (via 5-point scale) within the first survey only.

### Data management and analysis

Quantitative data will be downloaded from SurveyMonkey, imported into Statistical Package for the Social Sciences (SPSS) for analysis, cleaned, and subjected to quality checks. Descriptive statistics will be computed to describe the sample at baseline and to report on feasibility and acceptability outcomes. Categorical variables will be described using proportions and frequencies, and continuous variables with means and standard deviations (or with medians and interquartile ranges for data that are not normally distributed). CIs will be reported along with point estimates for each outcome.

Audio recordings from qualitative interviews will be transcribed verbatim, imported into NVivo for analysis, and coded using a hybrid approach of deductive and inductive reflexive thematic analysis [62].

Additional analyses (i.e., descriptive analyses, visual inspection) will be performed to describe overall levels and the extent to which patient-reported outcomes and putative mechanisms of psychosocial outcomes (i.e., anticipated primary and secondary definitive trial outcomes, respectively) change. Additionally, although exploratory, multilevel modeling will be used to estimate change in primary and secondary outcomes. Restricted Maximum Likelihood will be used instead of Full Maximum Likelihood because Restricted Maximum Likelihood has been shown to lead to better estimates with smaller sample sizes. Models will be estimated with no Level-2 covariates to maximize power. This said, effect sizes (e.g., measures of variance explained, measures of standardized effect size) will be reported for primary and secondary outcomes as this was a feasibility study that was not designed to test the efficacy of yoga. Because there are a number of ways to approach multilevel modeling and each model tested proceeds by estimating and comparing a series of unconditional and conditional models, full technical details and estimation methods will be described when reporting results.

Finally, once the main analyses are conducted to address the study aims, exploratory analyses may be undertaken to address subsequent research aims that will make unique theoretical and empirical contributions.

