### Sample size

A conventional power calculation was inappropriate for this feasibility study given the novel nature of delivering the program at the ORCF [45, 46]; rather, the target sample size was 20 participants based on end-user recommendations and pragmatic considerations. During the co-creation process, end-users recommended that class size be capped at 7 participants per program/group to allow the instructor to provide adequate feedback to participants, which was increased to 10 per program to account for up to 30% attrition based on the research team’s previous experience delivering group-based physical activity programs. In addition, end-users recommended running programs in the morning and evening to accommodate varying scheduling needs (e.g., energy levels, work). Pragmatically, due to the group-based nature of the program, the novelty of the program, and the context of the study (i.e., Covid-19-related shifts in lifestyles, priorities, and preferences), it was necessary to establish recruitment and enrolment rates as well as acceptability of novel program features prior to committing resources to run multiple iterations of the program. Thus, a SSRD was chosen as the study design wherein an appropriate sample size is generally small (e.g., range from 1 to 13 [32, 47]). Repeated assessments helped to ensure there were a sufficient number of data points to perform statistical analyses with sufficient power [32]. See Feasibility Outcomes for pertinent confidence intervals (CI).

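### The plan sets aside full ML for REML yet compares unconditional with conditional models; if that comparison is likelihood-based, REML values are not comparable and can depend on the unit of time

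*Protocol article*

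**What the plan says.** All of the relevant text is in the protocol article, section *Data management and analysis*.

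- Estimator: "Restricted Maximum Likelihood will be used instead of Full Maximum Likelihood". The reason given is that "Restricted Maximum Likelihood has been shown to lead to better estimates with smaller sample sizes".
- Predictors: "Models will be estimated with no Level-2 covariates to maximize power".
- Procedure: "each model tested proceeds by estimating and comparing a series of unconditional and conditional models".
- Status: "although exploratory, multilevel modeling will be used to estimate change in primary and secondary outcomes".
- Output: "effect sizes (e.g., measures of variance explained, measures of standardized effect size) will be reported for primary and secondary outcomes".
- Deferral: "full technical details and estimation methods will be described when reporting results".

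No criterion for comparing models is named, no rule for keeping or dropping a term is given, and no unit of time is stated. Under *Sample size*, "the target sample size was 20 participants based on end-user recommendations and pragmatic considerations". *Trial design* gives each person 3 to 5 weekly baseline surveys, 3 program surveys and 3 follow-up surveys. The models are meant for six patient-reported outcomes and three putative mechanisms.

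**The concern.** With no Level-2 covariates, a conditional model can differ from an unconditional one mainly through Level-1 terms. In this baseline, program and follow-up design those are time and phase, and both enter as fixed effects. If *unconditional* is meant as a growth model that already contains time, the added terms are still Level-1 fixed effects.

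The restricted likelihood contains a term in the fixed-effect design matrix. Two REML deviances from models with different fixed effects therefore do not measure fit on a common scale, and AIC and BIC inherit the problem. Full ML lacks that term and permits the comparison, but it is the estimator the text sets aside. The reason given for REML concerns the quality of estimates in small samples, which is sound, and does not address model comparison.

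At stake is whether a term for change over time or phase appears in the model reported for an outcome. The fourth study aim is to estimate program effects, and *Deliverables and implications* says these data will support the design of a future powered trial.

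**Working it through.** The plan states no figure here, so there is none to reproduce. The check is in two parts: one exact, one illustrative.

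**1. Exact effect of the time unit.** For N records, p fixed effects, design matrix X, covariance V and residuals r from the fitted fixed effects:

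- ML deviance = log|V| + r'V⁻¹r + N·log(2π)
- REML deviance = log|V| + r'V⁻¹r + log|X'V⁻¹X| + (N − p)·log(2π)

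Multiply the time column by c. The fitted values, r and V do not change, but |X'V⁻¹X| is multiplied by c². The REML deviance of the time model rises by 2·ln(c). The ML deviance does not change, and neither does the model without time.

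- Weeks to days, c = 7: 2·ln 7 = 2 × 1.9459 = 3.892. The chi-square cut-off on 1 df at 5% is 3.841.
- Weeks to years, c = 1/52: 2·ln(1/52) = −2 × 3.9512 = −7.902, a shift in the opposite direction.

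These shifts require no assumption about variances or slopes.

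**2. Illustration on the protocol's schedule.**

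Inputs from the article: 20 people; 3, 4 or 5 baseline surveys; program surveys at weeks 1, 6 and 12; follow-up surveys 1, 4 and 8 weeks after the program, coded as weeks 13, 16 and 20. With 7, 7 and 6 people in the three baseline groups, the number of records is 7×9 + 7×10 + 6×11 = 63 + 70 + 66 = 199.

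Assumptions, none of them given in the article: random-intercept model, between-person SD 10, residual SD 6, linear slope 0, 0.10 or 0.15 points per week. An intercept-only model is compared with a linear-time model.

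Deviance difference (intercept-only minus time) in one simulated data set:

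| Time unit | REML | ML |
|---|---|---|
| Weeks | −3.793 | 0.386 |
| Days | −7.684 | 0.386 |

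By the formula above, the same data coded in years would give a REML difference of −3.793 + 7.902 = 4.109, which exceeds 3.841. The unit alone could therefore turn a rejection of the time model into its acceptance, in data where ML shows almost no gain.

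Share of 300 simulated data sets in which the difference exceeded 3.841:

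| Slope per week | ML | REML, weeks | REML, days | Weeks and days disagree |
|---|---|---|---|---|
| 0 | 4.0% | 0% | 0% | 0% |
| 0.10 | 48.7% | 18.0% | 6.7% | 11.3% |
| 0.15 | 80.7% | 50.0% | 25.3% | 24.7% |

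The largest Monte Carlo standard error is √(0.5 × 0.5 / 300) = 2.9 percentage points. The ML test is close to its nominal 5% at slope 0. The REML rates follow the unit.

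**The case against.** The strongest reply is that the article never says the models will be compared by likelihood. It speaks of comparing, not of choosing, and names no deviance, likelihood-ratio test, AIC or BIC. It does list variance explained among the outputs. That quantity comes from comparing variance components between an unconditional and a conditional model, which can be done under REML and does not depend on the unit. Wald, t or F tests of fixed effects under REML are also sound, as is a REML comparison of models that differ only in random effects. All of this stands. A reader might infer that the planned comparison is invalid; the document supports only that it would be invalid if it were likelihood-based.

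The article also defers technical details and estimation methods to the results report, which leaves room to use ML for the comparison step. Leaving details to another document is no fault in an article. What remains is that the article makes a positive choice against ML in the same paragraph as the comparison step, without limiting that choice to the final estimates.

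The weeks-or-days problem needs a continuous time predictor, and none is specified. A phase indicator has no such unit. This also stands, although REML deviances with and without phase are still not comparable. Recoding one 0/1 indicator as −1/+1 doubles its scale and shifts the REML deviance by 2·ln 2 = 1.39.

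Finally, a reader might infer from the table that REML biases the comparison towards finding no change. That holds for weeks and days under the assumed values, but the shift to years goes the other way. The error is arbitrary in direction.

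**Conclusion.** The point holds in conditional form. The plan sets aside full ML while planning to compare models that differ mainly in fixed effects. Under any deviance, likelihood-ratio, AIC or BIC criterion, that combination gives values that are not comparable. The size of the unit dependence is exact: 3.89 deviance points for weeks against days, set against a cut-off of 3.84. The simulated rates are illustrations that rest on the assumed SDs, slopes and random-intercept form.

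The consequence is limited. Estimates and standard errors from a given REML model are not affected. A reader might infer that the whole aim of estimating program effects rests on this comparison; the document does not support that, because it also plans descriptive analysis, visual inspection and effect sizes, and calls the modelling exploratory. The primary outcomes (feasibility, acceptability and fidelity) are untouched. Severity is minor to moderate.

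**What to change.** Name the comparison criterion and add one sentence, for example: *Any likelihood-based comparison of models that differ in fixed effects will use full maximum likelihood; the reported model will then be refitted by REML, and REML will be used to compare random-effect structures only where the fixed effects are the same.* An equally sound alternative is to state that fixed effects will be judged by Wald or F tests under REML, with no comparison of REML deviances across different fixed effects.

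The cost is one sentence and, for the first option, one extra model fit per comparison. The stated preference for REML in small samples is kept where its rationale applies, in the final estimates. Since the technical details are to be given with the results, the sentence can be settled in the analysis plan before the models are run.

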## Ethics and dissemination

### Research ethics approval and protocol amendments

Ethics approval for the yoga program protocol was granted by the Ottawa Health Science Network Research Ethics Board on September 27, 2022 (file no.: 20220544-01H) and by the University of Ottawa’s Office of Research Ethics and Integrity on November 11, 2022 (file no.: H-10–22-8671). The trial was registered with the ClinicalTrials.gov database (no.: NCT05610982) on November 3, 2022. Any important protocol modifications (e.g., changes to eligibility criteria, recruitment procedures) will be reported promptly to relevant parties (e.g., team members, Institutional Review Boards, trial registry) and will be reported in forthcoming publication(s).

### Consent and confidentiality

Verbal informed consent was obtained from participants over the phone prior to data collection, and the yoga instructor prior to completing the interview. All data (i.e., interview recordings/transcripts, survey responses) are considered confidential and electronic files containing personal information can only be accessed by the investigators and study staff who sign a confidentiality form. A unique code is produced for each participant and used on all corresponding documentation and files to ensure anonymity. Furthermore, personal information that may enable participants to be identified will be removed from interview transcripts upon transcription.

### Access to data

Data sharing is restricted. No data will be deposited within public data repositories as participants and the yoga instructor were assured that their data would be kept private and confidential to the extent permitted by law, and that only the research team would have access to their data. De-identified electronic files containing quantitative and qualitative data are only to be shared with the research team for analysis. All quantitative and qualitative electronic data files are password-protected and stored on password-protected computers/laptops, a shared drive/server (i.e., The Ottawa Hospital server), and a web-based secure and encrypted data storage service (i.e., SurveyMonkey’s Canadian Data Centre); files will be kept for at least 5 years and possibly longer. Paper materials will be stored for 5 years following the completion of the study in locked cabinets in locked offices whose access is limited, after which point these will be destroyed securely (i.e., shredding).

### Dissemination plans

Study results will be shared with academic audiences via presentations at scientific meetings and publications in peer-reviewed journals. Results will be submitted to ClinicalTrials.gov no later than 1 year after study completion. To facilitate communication of results to non-academic audiences, presentations will be made to the ORCF board of directors and results will be presented in a publicly available report on the ORCF website. In addition, results will be shared via social media and a video summarizing the trial will be posted on the corresponding author’s website. As well, yoga instructors interested in using the instructor guidebook will be able to request access through the corresponding author’s website.

## Discussion

Yoga is a promising form of physical activity that can support psychosocial outcomes for women diagnosed with cancer when practiced regularly and safely [18]. Yet, most programs have some form of disconnect between program characteristics and participants’ needs [19]; thus, highlighting the need to co-create programs with end-users (i.e., yoga instructors, adults diagnosed with a gynecologic cancer). Prior to a definitive trial to assess the effects of the program and effort to scale up implementation, it was necessary to assess the feasibility, acceptability, and fidelity of the study methods and program as well as potential benefits of the program to ensure viability and value.

## Deliverables and implications

The results of the study described in this article will provide valuable knowledge and insight to refine the current program, materials to facilitate its delivery as planned (i.e., instructor guidebook), and the methods used to evaluate it. Further, data on patient-reported outcomes and putative mechanisms of change will support the design of a sufficiently powered future trial. In the long term, if successful, the deliverable of this study will be a yoga program suitable for delivery in a community setting. This program will aim to provide yoga instructors and community organizations with a resource for adults diagnosed with a gynecologic cancer to support bio-psycho-social outcomes related to QoL.

## Data Availability

Not applicable.

## Abbreviations

QoL: Quality of life
ORCF: Ottawa Regional Cancer Foundation
SSRD: Single-subject research design
SPIRIT: Standard Protocol Items: Recommendations for Interventional Trials
CONSORT: Consolidated Standards of Reporting Trials
CLARIFY: Checklist Standardising the Reporting of Interventions For Yoga
SPSS: Statistical Package for the Social Sciences
